### Intervention protocol

#### Experimental group interventions

In this study, patients in the experimental group will receive TFRL-IMT in addition to conventional treatment. TFRL-IMT will be administered using the inspiratory muscle training module of a portable pulmonary function testing device (X1, Seck Medical Devices Co., Ltd., Xiamen, China). The initial training load will be set at 30% of the subject’s MIP, which will be measured using the device’s built-in function. During the study period, MIP will be measured weekly, and the training load will be adjusted to 30% of the current MIP. Additionally, resistance will be gradually increased by 5% per week until 60% of MIP is reached and maintained, depending on the patient’s tolerance.

The training programme will last for 3 weeks, during which patients will undergo two sessions per day, each comprising five sets of six maximal inspiratory efforts with a one-minute rest between sets. During each session, the patient’s tracheal cannula will be connected to the device valve via a specialized connecting tube, and the patient will be instructed to inhale as forcefully and rapidly as possible, followed by slow exhalation. All training will be conducted under the supervision of healthcare professionals to ensure training quality and patient safety. The rehabilitation therapist will document the actual load, completion status, and any adverse events during each training session.

In patients with concurrent respiratory infections, appropriate antibiotics will be administered based on clinical manifestations and sputum culture results. In patients with thick sputum, nebulized salbutamol (2.5 mg) combined with ipratropium bromide (0.5 mg) will be administered three times daily at 8:00 a.m., 12:00 p.m., and 8:00 p.m.

To evaluate the efficacy and safety of the intervention, MIP values will be measured before and after training using the same portable pulmonary function device. Simultaneously, vital signs such as including heart rate, blood pressure, respiratory rate, and oxygen saturation will be continuously monitored.

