#### Control group interventions

Patients in the control group will receive comprehensive conventional treatment, consisting of four main components: respiratory exercise, pharmacotherapy, airway management and positional management.

Respiratory function exercises will be conducted for 15 min twice daily at fixed time intervals (8:00–9:00 a.m. and 4:00–5:00 p.m.). The regimen will include deep breathing exercises, thoracic mobility training, and sputum expectoration training. During deep breathing exercises, patients will be instructed to inhale slowly and deeply through a tracheotomy cannula over 3 s, hold their breath for 2 s, and exhale slowly over 4 s. Each session will consist of 10 repetitions per set, with three sets completed and a 1 min rest between sets. Patients will be guided by a therapist to perform expansion movements of the upper, middle, and lower thoracic segments, five times for each segment. Sputum clearance training will include postural drainage, mechanical vibration expectoration, and instruction in effective coughing techniques, with each method applied for 5 min.

The pharmacological treatment protocol will be consistent with that of the experimental group, with appropriate antibiotics selected based on patients’ clinical manifestations and sputum culture results. For patients with viscous sputum, nebulized salbutamol (2.5 mg) combined with ipratropium bromide (0.5 mg) will be administered three times daily, at 8:00 a.m., 12:00 p.m., and 8:00 p.m. In addition, airway humidification with 5–10 mL of saline will be performed every 4 h to prevent sputum crust formation.

Airway management will involve assessing the need for suctioning every 4–6 h, with suctioning performed as necessary. The inner cannula of the tracheotomy tube will be changed twice daily, at 8:00 a.m. and 6:00 p.m., under strict aseptic conditions. Tracheotomy care will include daily cleaning of the skin around the tracheotomy site with 0.9% saline, and monitoring for signs of infection.

Position management will involve repositioning every 2 h to avoid maintaining the same position for long periods of time. Progressive positioning and limb mobility exercises will be performed for 15 min, twice daily.

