All routine treatments will be delivered by medical personnel who have received standardised training. During treatment, healthcare professionals will closely monitor patients’ vital signs and immediately discontinue the intervention if any discomfort occurs. During the study period, patients will be prohibited from engaging in any other form of respiratory muscle training, adding new medications that may influence respiratory muscle function (e.g., systemic corticosteroids, neuromuscular blockers, or long-acting sedatives), or participating in other clinical trials that could affect respiratory function.

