#### Outcome measures

The timetable for enrolment, intervention, and assessment is presented in Table 1.

**Table 1 tab1:** SPIRIT schedule of enrollment, interventions and assessment.

Study phase	Screening	Baseline	Intervention period			Follow-up period		
Visit	V0	V1	V2	V3	V4	V5	V6	V7
Time window	−7d ~ 0d	−24 h	Week 1	Week 2	Week 3	±2 h	±1d	±7d
Basic information								
Informed consent	√							
Demographics	√							
Medical history	√							
Inclusion/exclusion	√							
Primary outcome								
Decannulation readiness^a^			√	√	√			
Decannulation outcome					√	√	√	√
Secondary outcomes								
Diaphragm function^b^		√			√			
Respiratory parameters^c^		√			√			
Clinical outcomes^d^					√	√	√	√
Quality of life assessment^e^		√			√			√
Safety assessment								
Adverse events		√	√	√	√	√	√	√

V0 (screening): within 7 days before enrollment; V1 (baseline): within 24 h pre-intervention; V2-V4 (intervention period): ±1 day; V5 (post-decannulation 72 h): ±2 h; V6 (post-decannulation 1 week): ±1 days; V7 (3 months follow-up): ±7 days.

a Decannulation preparation assessment will include: The amount of secretion is small and the patient is able to clear it effectively; Effective cough with a peak cough flow rate >160 L/min; no hypoxaemia (SpO₂ ≥ 92%), respiratory distress, or decrease in the level of consciousness during the 24 h consecutive tracheostomy tube occlusion test; Swallowing function is normal.

b Diaphragmatic function assessment will include: diaphragmatic mobility and diaphragmatic thickness.

c Respiratory function parameters include: MIP, FVC, PEF, FEV1.

d Clinical outcome evaluation will include: length of hospital stay, rate of respiratory-related complications, and rate of reintubation within 72 h of decannulation.

e Quality of life assessment includes: EQ-5D-5L Health-Related Quality of Life Questionnaire, The Breathing Difficulty Assessment (Borg Scale), and The Hospital Anxiety and Depression Scale (HADS).

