### Data management

The data collection process for this study will be as follows: First, the study data will be recorded in the Electronic Medical Record (EMR) system, and trained researchers will transcribe the eligible data from the EMR into the standardized electronic Case Report Form (eCRF) based on the inclusion criteria. A complete audit trail will be maintained for all data entry and modification operations to comply with the requirements of International Council for Harmonisation—Good Clinical Practice (ICH-GCP).

This study employs a three-tiered data quality control strategy: first, source data validation by comparing the consistency between entries in the EMR and the eCRF; second, real-time validation built into the system, which employs logic checking and range validation tools to promptly identify data inconsistencies; and third, cyclical quality assessment involving weekly data quality reports to monitor data status. A full-time data manager and statistician supervised data collection to ensure strict adherence to the study protocol and regulatory standards. Upon completion of patient follow-up, original data will be digitised and archived, and the eCRF retained until data lock.

In addition, An independent Data Safety Monitoring Board (DSMB) will be established, consisting of neurologists, respiratory therapists, and statisticians. The DSMB will perform biannual blinded reviews to assess data integrity, quality, and potential safety concerns, and will independently provide recommendations to the study leaders based on these findings, thereby ensuring the safety and scientific validity of the study.

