### Statistical analysis

The effect of the intervention will be evaluated based on both intention-to-treat (ITT) and per-protocol (PP) principles. Between-group comparisons for the primary outcome (decannulation success rate) will be conducted using the chi-square test or Fisher’s exact test, along with calculation of relative risk (RR), absolute risk reduction (ARR), and number needed to treat (NNT). Multivariate logistic regression analysis will be used to adjust for prespecified covariates such as age, sex, and stroke type. Between-group comparisons for continuous secondary outcomes will be conducted using t-tests or Mann–Whitney U tests. Repeated measures data will be analyzed using mixed linear models. Categorical secondary outcomes will be analyzed using the same approach as for the primary outcome. Time-to-event outcomes will be analyzed using Kaplan–Meier survival analysis and Cox proportional hazards regression models.

Missing data will primarily be handled using mixed-effects models under the missing at random (MAR) assumption, with multiple imputation and complete case analysis conducted as sensitivity analyses. Prespecified subgroup analyses will include factors such as stroke type and age, with effect heterogeneity evaluated using interaction terms and controlled for multiple comparisons via the Benjamini-Hochberg method. Sensitivity analyses will also include comparisons between ITT and PP outcomes, comparisons of different statistical methods, and assessment of covariate selection strategies.

All analyses will be performed using R software (version 4.2.0), employing two-sided tests with a significance level of 0.05. The analysis will be conducted by an independent statistician, and the analysis plan was pre-specified before enrollment of the first patient to ensure reproducibility and transparency. Categorical variables will be presented as frequencies (percentages), and group comparisons will be conducted using the chi-square test or Fisher’s exact test. Continuous variables will be presented as mean ± standard deviation or median (interquartile range), depending on distributional characteristics. Group comparisons will be conducted using the t-test or Mann–Whitney U test. Safety analyses will include the incidence of adverse events and between-group comparisons.

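### Adverse events are recorded at every training session only for TFRL-IMT, and two of seven safety visits exist only after decannulation, so the between-group comparison is open to ascertainment bias

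*Protocol article*

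**What the plan says.** **Recording in the TFRL-IMT arm.** Under Experimental group interventions: "The rehabilitation therapist will document the actual load, completion status, and any adverse events during each training session". On frequency: "The training programme will last for 3 weeks, during which patients will undergo two sessions per day". The section also states that "patients in the experimental group will receive TFRL-IMT in addition to conventional treatment", so this log comes on top of the care that both arms share. Randomisation and blinding concedes that treatment providers cannot be blinded.

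**Recording in the control arm.** Under Control group interventions: "Respiratory function exercises will be conducted for 15 min twice daily at fixed time intervals". For routine treatment in general, "healthcare professionals will closely monitor patients’ vital signs and immediately discontinue the intervention if any discomfort occurs". That sentence covers monitoring and stopping. No adverse-event record is stated for these sessions.

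**Scheduled assessments.** The adverse-event row of Table 1 has seven ticks, V1 to V7, with no split by arm. V1 is baseline and V2 to V4 are the weekly intervention visits. V5 is timed at 72 hours after decannulation, and the next visit is labelled "V6 (post-decannulation 1 week". V7 falls 3 months after the intervention whatever the tube status (Secondary outcomes).

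**Respiratory complications.** Secondary outcomes has these extracted from the electronic medical record, without distinction by arm.

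**Analysis.** Under Statistical analysis: "Safety analyses will include the incidence of adverse events and between-group comparisons".

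**The concern.** A comparison of incidence between arms is fair only if an event has about the same chance of being recorded in each arm. As written, that chance differs in two ways.

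First, a therapist who knows the allocation is asked about twice a day to note any adverse event, in one arm only. That can pick up events caused by the device, which controls cannot have. It can also pick up background events, which controls have equally.

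Second, V5 and V6 depend on the primary outcome. A patient who keeps the tube has no scheduled visit in Table 1 between V4 (week 3) and V7 (3 months). If TFRL-IMT raises decannulation as expected, its arm gets more of these contacts.

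Both differences point towards more recorded events with TFRL-IMT. At stake is the safety conclusion, not the primary outcome: an apparent excess with TFRL-IMT could not be separated from closer observation. Events never recorded in controls cannot reliably be recovered at analysis.

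**Working it through.** The document gives no adverse-event rate or other safety figure, so there is none to reproduce. What can be done is to count recording occasions and then show how far unequal capture could move a ratio.

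**1. Session logs (TFRL-IMT only).** Inputs: 2 sessions per day and 3 weeks (Experimental group interventions). Training days per week are not stated, so 5 to 7 is assumed.
- 5 days: 2 × 5 × 3 = 30 logs per patient
- 6 days: 2 × 6 × 3 = 36
- 7 days: 2 × 7 × 3 = 42
- Control arm, as stated: 0

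**2. Scheduled assessments.** Inputs: 30 patients per arm and planned success of 80% against 50% (Sample size calculation). The success rates stand in for decannulation rates, which is an approximation because a failed decannulation also starts the V5/V6 clock.
- Patients with V5/V6: 30 × 0.80 = 24 against 30 × 0.50 = 15
- V5/V6 contacts: 2 × 24 = 48 against 2 × 15 = 30
- Mean adverse-event assessments per patient: 5 + 2 × 0.80 = 6.6 against 5 + 2 × 0.50 = 6.0

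**3. Effect of V5/V6 alone.** Assume the same probability q of detecting at least one event at each visit in both arms. The probability of any recorded event is d × [1 − (1 − q)^7] + (1 − d) × [1 − (1 − q)^5], where d is the proportion decannulated.

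| q (assumed) | d = 0.80 | d = 0.50 | Ratio |
|---|---|---|---|
| 0.05 | 0.287 | 0.264 | 1.09 |
| 0.10 | 0.499 | 0.466 | 1.07 |
| 0.20 | 0.767 | 0.731 | 1.05 |

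**4. Effect of unequal capture through the session log.** Assume equal true risk p in both arms, full capture with TFRL-IMT and capture c in controls. The observed ratio is p / (p × c) = 1/c, whatever p is.

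| c (assumed) | Observed at p = 0.30 | Ratio |
|---|---|---|
| 0.9 | 30% against 27% | 1.11 |
| 0.7 | 30% against 21% | 1.43 |
| 0.5 | 30% against 15% | 2.00 |

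Nothing in the document fixes p, q or c. The tables show that the decannulation-dependent visits matter little on their own and that the session log could matter more.

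**The case against.** Four arguments weigh against the point.

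**The log covers an exposure that controls do not have.** Recording load, completion and events at each device session is ordinary device-safety practice, and no session log is stated for the conventional exercises in either arm. This stands for device-related events. It does not remove the problem, because the log takes in any adverse event, is kept by an unblinded provider, and feeds a between-group comparison with nothing shown to separate its events from the rest.

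**Most safety assessment is common to both arms.** Five of the seven visits apply to every patient, adverse events at evaluations are recorded without regard to arm, and complications come from the medical record in both arms. This largely stands. A reader might infer that adverse events are sought only at visits that follow decannulation, or that complications in patients who keep the tube go unseen. Table 1 and the record extraction do not support either reading, at least while patients are in hospital.

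**The control-arm gap is an argument from silence.** A journal article condenses a fuller protocol, which may hold a control-arm form. This limits confidence. Still, the article writes the rule for one arm and describes the other arm's sessions in detail without it.

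**The direction is against the new treatment.** The likely error overstates harm from TFRL-IMT rather than concealing it. That is fair, but a false safety signal is still an error.

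A reader might also infer that the DSMB could not see an imbalance, because "The DSMB will perform biannual blinded reviews to assess data integrity, quality, and potential safety concerns". That would follow only if the board saw pooled data. Blinded review may equally mean arms coded A and B, which would show one: 8/30 against 1/30 gives Fisher p = 0.026. The document does not say which is meant.

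**Conclusion.** The point holds in limited form. Followed as written, the comparison of adverse-event incidence rests on recording that differs by arm (the session log) and by primary outcome (V5 and V6). It is open to ascertainment bias towards more recorded events with TFRL-IMT. It cannot be said that the comparison is biased by a known amount.

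What can be counted is 30 to 42 additional recording occasions per TFRL-IMT patient during the intervention, and about 0.6 additional scheduled assessments (6.6 − 6.0). If V5/V6 were the only difference, the ratio would shift by roughly 5% to 9% under the assumed detection rates. The session log is the main source, and its effect depends on control-arm capture, for which the document gives no figure. The conclusion assumes that no matching control-arm record exists in the full protocol or case report form; if one does, the main part of the concern falls away.

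**What to change.** 1. Use the same adverse-event form at the conventional exercise sessions already held in both arms. If the full protocol already provides this, state it.
2. Compare adverse events and respiratory complications over one calendar window for all randomised patients, from randomisation to the 3-month follow-up, using events from recording occasions common to both arms.
3. Report events detected only at TFRL-IMT sessions, or only at V5/V6, in a separate table and in full. Dropping them would lose the events most attributable to the device.

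The cost is slightly more recording by staff who are already present, and two safety tables instead of one. No treatment changes.

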#### Control group interventions

Patients in the control group will receive comprehensive conventional treatment, consisting of four main components: respiratory exercise, pharmacotherapy, airway management and positional management.

Respiratory function exercises will be conducted for 15 min twice daily at fixed time intervals (8:00–9:00 a.m. and 4:00–5:00 p.m.). The regimen will include deep breathing exercises, thoracic mobility training, and sputum expectoration training. During deep breathing exercises, patients will be instructed to inhale slowly and deeply through a tracheotomy cannula over 3 s, hold their breath for 2 s, and exhale slowly over 4 s. Each session will consist of 10 repetitions per set, with three sets completed and a 1 min rest between sets. Patients will be guided by a therapist to perform expansion movements of the upper, middle, and lower thoracic segments, five times for each segment. Sputum clearance training will include postural drainage, mechanical vibration expectoration, and instruction in effective coughing techniques, with each method applied for 5 min.

The pharmacological treatment protocol will be consistent with that of the experimental group, with appropriate antibiotics selected based on patients’ clinical manifestations and sputum culture results. For patients with viscous sputum, nebulized salbutamol (2.5 mg) combined with ipratropium bromide (0.5 mg) will be administered three times daily, at 8:00 a.m., 12:00 p.m., and 8:00 p.m. In addition, airway humidification with 5–10 mL of saline will be performed every 4 h to prevent sputum crust formation.

Airway management will involve assessing the need for suctioning every 4–6 h, with suctioning performed as necessary. The inner cannula of the tracheotomy tube will be changed twice daily, at 8:00 a.m. and 6:00 p.m., under strict aseptic conditions. Tracheotomy care will include daily cleaning of the skin around the tracheotomy site with 0.9% saline, and monitoring for signs of infection.

Position management will involve repositioning every 2 h to avoid maintaining the same position for long periods of time. Progressive positioning and limb mobility exercises will be performed for 15 min, twice daily.

All routine treatments will be delivered by medical personnel who have received standardised training. During treatment, healthcare professionals will closely monitor patients’ vital signs and immediately discontinue the intervention if any discomfort occurs. During the study period, patients will be prohibited from engaging in any other form of respiratory muscle training, adding new medications that may influence respiratory muscle function (e.g., systemic corticosteroids, neuromuscular blockers, or long-acting sedatives), or participating in other clinical trials that could affect respiratory function.

#### Outcome measures

The timetable for enrolment, intervention, and assessment is presented in Table 1.

**Table 1 tab1:** SPIRIT schedule of enrollment, interventions and assessment.

Study phase	Screening	Baseline	Intervention period			Follow-up period		
Visit	V0	V1	V2	V3	V4	V5	V6	V7
Time window	−7d ~ 0d	−24 h	Week 1	Week 2	Week 3	±2 h	±1d	±7d
Basic information								
Informed consent	√							
Demographics	√							
Medical history	√							
Inclusion/exclusion	√							
Primary outcome								
Decannulation readiness^a^			√	√	√			
Decannulation outcome					√	√	√	√
Secondary outcomes								
Diaphragm function^b^		√			√			
Respiratory parameters^c^		√			√			
Clinical outcomes^d^					√	√	√	√
Quality of life assessment^e^		√			√			√
Safety assessment								
Adverse events		√	√	√	√	√	√	√

V0 (screening): within 7 days before enrollment; V1 (baseline): within 24 h pre-intervention; V2-V4 (intervention period): ±1 day; V5 (post-decannulation 72 h): ±2 h; V6 (post-decannulation 1 week): ±1 days; V7 (3 months follow-up): ±7 days.

a Decannulation preparation assessment will include: The amount of secretion is small and the patient is able to clear it effectively; Effective cough with a peak cough flow rate >160 L/min; no hypoxaemia (SpO₂ ≥ 92%), respiratory distress, or decrease in the level of consciousness during the 24 h consecutive tracheostomy tube occlusion test; Swallowing function is normal.

b Diaphragmatic function assessment will include: diaphragmatic mobility and diaphragmatic thickness.

c Respiratory function parameters include: MIP, FVC, PEF, FEV1.

d Clinical outcome evaluation will include: length of hospital stay, rate of respiratory-related complications, and rate of reintubation within 72 h of decannulation.

e Quality of life assessment includes: EQ-5D-5L Health-Related Quality of Life Questionnaire, The Breathing Difficulty Assessment (Borg Scale), and The Hospital Anxiety and Depression Scale (HADS).

